### Concealment mechanism {16b}

The implementation of the allocation sequence is done by the REDCap® software. Also, there is a datasheet information available to be used as a guideline for the investigators.

### Implementation {16c}

The enrolment of the patients will be done by the involved physicians in the study. Each participant center has a research team to carry out the rest of the activities of the project and a central Contract Research Organization (CRO) gives support for all of them.

## Assignment of interventions: blinding

### Who will be blinded {17a}

This is an open label trial.

### Procedure for unblinding if needed {17b}

Unblinding is not needed.

## Data collection and management

### Plans for assessment and collection of outcomes {18a}

Assessment and collection of baseline, and other trial data, including outcomes measures, will be performed by the centers research teams using an electronic data collection notebook (REDCap®)

### Plans to promote participant retention and complete follow-up {18b}

Patients’ adherence to protocol will be closely checked during the CRO’s monitoring visits. The protocol includes a form with a list of outcome data to be collected for participants who discontinue or deviate from intervention protocols. To improve retention and minimize loss to follow-up, investigators are asked to contact patients when they do not attend the scheduled visits and provide them a new appointment.

### Data management {19}

CRO staff will train research teams on data entry and storage on the electronic database collection notebook (REDCap®) and promote data quality checks.

### Confidentiality {27}

The Health Authority, the Ethics Committee, and the medical monitors and/or auditors designated by the Promoter may access to data base in each center, in order to verify the accuracy and reliability of the data provided by the principal investigator about the subjects participating in the trial. The designated monitors and/or auditors will work according to the provisions of the Articles 39 and 40 of the Spanish Law (RD 1090/2015) and the Principal Investigator must ensure that monitors, auditors, or CROs respect the confidentiality rules of any information about the subjects of the study. Each center will facilitate access to this data to its Ethics Committee and to the inspectors of the competent health authorities.

### Plans for collection, laboratory evaluation, and storage of biological specimens for genetic or molecular analysis in this trial/future use {33}

The protocol includes a description of the study plans for collection, laboratory evaluation, and storage of biological specimens for laboratory analysis in the current trial and for future use in ancillary studies. The use of the samples in ancillary studies requires the sign of an additional informed consent. The collected samples will be: plasma for all patients and whole blood and peripheral blood mononuclear cell samples for ancillary studies. All the biological samples will be stored at − 80 °C. Most Spanish hospitals have their own biobank to storage the samples collected. All biobanks must fulfill the requirements of the Spanish Law for these facilities.

## Statistical methods

### Statistical methods for primary and secondary outcomes {20a}

The primary efficacy analysis will be the comparison of the proportion of cancers diagnosed at an early stage (1 and 2) in each group following the principle of intent to screen, defined as patients who accept to participate in the study and sign the informed consent, regardless of whether they are subsequently excluded due to loss of follow-up, non-adherence to study procedures, unwillingness to remain in the study, death, etc. A per protocol analysis including patients who complete the study will also be performed. A sample size of 2319 patients in each group has been calculated (expected incidence of early cancer 2% and 1% in enhanced and conventional groups, respectively; statistic power 80%; losses to follow-up 20%). Missing observations in the variables will be ignored in the analysis.

The secondary efficacy analysis will include the comparison of the incidence of cancer at any stage or unknown stage and the incidence of new cases of cancer diagnosed at stage 1 and 2 related to all new cases of cancer diagnosed.

The secondary safety analysis will compare the number of unnecessary invasive procedures, the rate of adverse events and severe adverse events, and overall mortality and mortality from cancer in both groups.

The secondary cost-utility analysis will be carried out following the recommendations of the guide for the economic evaluation of health technologies in Spain from the perspective of Spanish National Health System. The incremental cost-effectiveness ratio will be calculated, which is a measure of contrast between the increase in costs and the increase in effectiveness between the different screening alternatives compared. Statistical uncertainty will be expressed as the 95% confidence interval. Random samples of 100 patients from each group replaced 10,000 times will be projected on a graph to generate the increase in QALYs (quality-adjusted life year), the increase in costs, and the cost-effectiveness curve.

The analyses will be performed by a statistician blinded to patients’ allocation using the statistical packages SPSS® v.17 or higher, and R® 3.3 or higher. The statistical significance is set at *p* < 0.05.

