## Methods: participants, interventions, and outcomes

### Study setting {9}

The study will be carried in the framework of the Spanish network of AIDS research (CoRIS), including 30 centers, being all of them Spanish academic hospitals.

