### Outcomes {12}

Primary outcome: diagnosis with a new NADC at stage 1 or 2, overall and for the specific cancer sites: invasive malignancies of lung, anus, liver, cervix, breast, prostate, colorectal, ovary, and invasive melanomas of skin assessed through various exams, and compared as the proportion between intervention groups at 12, 24, and 36 months.

Secondary outcomes: (1) diagnosis with a new NADC at any stage or unknown stage, overall and for the specific cancer sites: invasive malignancies of lung, anus, liver, cervix, breast, prostate, colorectal, ovary, and invasive melanomas of skin assessed through various exams, and compared as the proportion between intervention groups at 12, 24, and 36 months; (2) diagnosis with new cases of cancer diagnosed at stage 1 and 2 related to all new cases of diagnosed cancer compared as the proportion between groups at 12, 24, and 36 months; (3) unnecessary invasive procedures (with non-diagnostic results) compared as the proportion in each treatment group at 12, 24, and 36 months; (4) adverse events and severe adverse events related to the study procedures compared as the rate in each treatment group at 12, 24, and 36 months, and (5) overall mortality and mortality from cancer at 12, 24, and 36 months.

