## Assignment of interventions: allocation

### Sequence generation {16a}

The study will be operated by an electronic data collection notebook (REDCap®). This software allows assigning random numbers to the recruited patients. Also, there is a plan restriction to ensure well-balanced proportions of patients and representation of genders per branch and center. Specifically, random allocation will be carried out in blocks of twenty patients with a 1:1 ratio to either intervention group in men and women .

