### Methods for additional analyses (e.g., subgroup analyses) {20b}

Subgroup analyses will be performed for: age groups every 5 years, sex, status of smoking, risk group, CD4 range, CD4 nadir, and HIV viral load. Sensitivity analysis will also be performed on the uncertain values of the model, taking the most pessimistic and optimistic assumptions about long-term survival of each tumor. Sensitivity analyses related to internal validity will also be carried out in the following variables: quality of life after positive screening and after the diagnosis of NADCs and radiation-induced cancer deaths. To analyze the generalizability of the results, sensitivity analyzes will be carried out in the operative mortality and in various costs, such as the costs of screening, follow-up LDCT, surgery, chemotherapy, radiotherapy, and management of incidental findings. A sensitivity analysis will also be carried out using an annual discount of 0 and 5%. The sensitivity analyzes will be carried out through a probabilistic sensitivity analysis, and the results will be presented as a dispersion analysis (cost-effectiveness plan) and the acceptability curve.

The same statistical packages SPSS® v.17 or higher, and R® 3.3 or higher will be used to carry with these subgroup analysis. The statistical significance is also set at *p* < 0.05.

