## Discussion

Related to general population, PLWH are at higher mortality risk due to screenable cancer [30]. Increased mortality can result from higher incidence or late diagnosis, the latter amenable to improved screening. However, the benefits and harms associated with cancer screening in PLWH are unclear and may differ compared with uninfected persons. This trial will help to determine whether the benefits of the enhanced screening outweigh the harms and if it is cost-effective for the Public Health Services.

Although the ideal outcome measure would be mortality due to cancer, with our sample size, we will not reach the number of patients needed to detect differences in mortality between both groups. Hence, we established as a main outcome measure the detection of a greater number of cancers in early stages. It is unlikely that a randomized controlled trial of screening will be conducted with enough power to determine the cancer mortality reduction among the HIV-infected population. This trial has other limitations. There could be differences in baseline NADCs screening in different centers. Attempts will be made to correct these differences by redefining the protocol of the control group using the baseline screening data of the baseline survey trying to unify the screening in that group. Additionally, as it is a controlled study with a parallel group, there may be a risk of benefit from the control group due to imitation of the intervention group. After the first interim data analysis and if strictly necessary, a historical control group can be included prior to the start of the intervention group.

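### As described, the primary comparison makes no use of the sex and centre factors on which allocation is balanced; stating a stratified analysis would be a small improvement that costs nothing

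*Protocol article*

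**What the plan says.** All references are to the protocol article.

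- **Allocation, Sequence generation {16a}.** The aim is that "there is a plan restriction to ensure well-balanced proportions of patients and representation of genders per branch and center". The operative sentence is narrower: "random allocation will be carried out in blocks of twenty patients with a 1:1 ratio to either intervention group in men and women". Sex is therefore a blocking factor. Centre is a stated aim of the restriction, but the sentence that gives the mechanism does not repeat it.
- **Centres, Study setting {9}.** The network is described as "including 30 centers, being all of them Spanish academic hospitals", which gives up to 30 × 2 = 60 sex-by-centre strata.
- **Primary analysis, Statistical methods {20a}.** "The primary efficacy analysis will be the comparison of the proportion of cancers diagnosed at an early stage (1 and 2) in each group", by intent to screen. Outcomes {12} adds that the result is "compared as the proportion between intervention groups at 12, 24, and 36 months". Neither section names a test or model, or calls the comparison adjusted or unadjusted.
- **Other uses of the factors, Methods for additional analyses {20b}.** "Subgroup analyses will be performed for: age groups every 5 years, sex, status of smoking, risk group", followed by HIV markers. Sex appears there as a subgroup factor. Centre appears in no analysis.
- **Centre differences, Discussion.** "There could be differences in baseline NADCs screening in different centers". The response is: "Attempts will be made to correct these differences by redefining the protocol of the control group using the baseline screening data".

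**The concern.** When allocation is balanced on a factor that predicts the outcome, the analysis should normally account for it. Otherwise the arms are more alike than the unstratified standard error assumes, so that standard error is slightly too wide and the test slightly conservative.

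Both factors plausibly predict the outcome here. Sex decides which primary-outcome sites can occur at all (prostate; cervix and ovary). Centre matters because the conventional schedule allows intervals of one to three years and makes PSA optional, so detection can differ between hospitals.

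What is at stake is some precision, and a comparison of participants within the same hospital and sex. The secondary outcomes that are likely to be commoner and to depend on local practice (invasive procedures, adverse events, costs) should gain more than the rare primary outcome.

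**Working it through.** **Inputs from the article.** 2% versus 1% early cancer, 80% power, a one-sided contrast, 20% loss, 2,319 per arm (Sample size {14}); significance at 0.05 ({20a}); 30 centres ({9}); blocks of 20, 1:1 ({16a}). The denominator is taken as participants, as in the sample size section.

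**Inputs that are assumptions.** The spread of risk between centres, the sex effect and the share of men. The article gives none of these, so ranges are shown.

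**1. The plan's own figure.** The usual unstratified formula is n = [z_α √(2p̄q̄) + z_β √(p₁q₁ + p₂q₂)]² / (p₁ − p₂)², with p̄ = 0.015.

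- One-sided 0.05: [1.645 × 0.1719 + 0.842 × 0.1718]² / 0.0001 gives 1,826. Dividing by 0.8 gives 2,283, which is 1.6% below 2,319.
- Two-sided 0.05 with no allowance for loss gives exactly 2,319.

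Either way, a formula without strata roughly or exactly returns the stated number. That fits an unstratified plan but does not prove one, because such formulas are often used to size stratified analyses too.

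**2. How thin the strata are.** Evaluable per arm: 2,319 × 0.8 ≈ 1,855. Expected events: 1,855 × 0.02 + 1,855 × 0.01 ≈ 56, over up to 60 strata. That is about one event per stratum or fewer, which Mantel-Haenszel methods can handle.

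**3. How much variance the strata can explain.** If centre log-risk has SD s, the share of binary variance lying between centres is about (exp(s²) − 1) p² / [p(1 − p)].

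- p = 1.5%, s = 0.5: 0.284 × 0.0152 = 0.4%.
- p = 1.5%, s = 1.0: 1.718 × 0.0152 = 2.6%.
- p = 10%, s = 0.5: 0.284 × 0.01 / 0.09 = 3.2%.
- p = 10%, s = 0.8: 0.896 × 0.01 / 0.09 = 10.0%.

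For a rare outcome there is little to gain, whatever the spread between centres.

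**4. Simulation of the primary outcome.** 10,000 trials per setting, 30 unequal centres × 2 sexes, 80% men assumed, exact 1:1 within strata. Power in %, unstratified z-test versus Mantel-Haenszel test:

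| Per arm | Centre SD (log-odds) / sex odds ratio | One-sided | Two-sided |
|---|---|---|---|
| 2,319 | 0 / 1 | 88.3 v 88.3 | 81.0 v 81.0 |
| 2,319 | 0.5 / 1.5 | 88.5 v 88.5 | 80.9 v 81.0 |
| 2,319 | 1 / 2 | 88.2 v 88.5 | 81.1 v 81.6 |
| 1,855 | 0 / 1 | 81.8 v 81.6 | 71.3 v 71.4 |
| 1,855 | 0.5 / 1.5 | 81.4 v 81.4 | 70.8 v 71.0 |
| 1,855 | 1 / 2 | 81.6 v 81.7 | 71.3 v 72.1 |

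Null rejection was 4.6–5.3% (unstratified) and 4.7–5.3% (stratified) one-sided, and 4.7–4.9% and 4.7–5.2% two-sided.

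A second simulation used real blocks of 20 (2,500 trials per setting, 3,710 evaluable in total, 18% women assumed). Two-sided power was 69.8 v 69.2 with no stratum differences, 72.1 v 72.3 with centre log-risk SD 0.5 and a sex risk ratio of 2, and 69.4 v 70.3 with centre SD 1.0. The simulation error of each figure is √(0.7 × 0.3 / 2,500) ≈ 0.9 points.

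**5. A commoner outcome.** For an assumed 10% outcome with centre log-SD 0.5–0.8 and 3,710 evaluable (10,000 trials), stratifying gained about 1–3 points of power. The unstratified test rejected a true null about 4.1–4.7% of the time, which is the mild conservatism expected from step 3.

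**The case against.** The strongest objection is that the article never says the comparison is unadjusted. A Mantel-Haenszel comparison would also fit the sentence in {20a}, and an article commonly leaves the test and covariates to an analysis plan. This stands: the silence is not an error, and the point can only be offered as an improvement to what is described.

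A reader might draw four stronger conclusions. The document supports none of them.

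- *That the plan fixes a crude analysis and so contradicts its own randomisation.* No test is named, and centre is an aim of the allocation rather than a confirmed stratum. If centre is not a formal stratum, a centre-stratified analysis is still valid.
- *That the result would be biased or the type I error inflated.* The simulations show neither. Any departure is towards conservatism.
- *That the trial changes its control protocol instead of stratifying.* The Discussion does not present the two as alternatives. Its concern is that usual screening differs between hospitals.
- *That stratifying would settle that concern.* It compares like with like within a centre. Where usual care is already close to enhanced screening, however, the contrast stays diluted, and the overall effect remains an average over differing control practices.

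The objection that the primary gain is negligible also largely stands. On the one-sided basis stated for the sample size, with 1,855 per arm, there is no visible gain. The larger gains for commoner outcomes rest on assumed event rates and centre spreads.

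**Conclusion.** The point holds as a low-severity, cost-free improvement. As described, the primary comparison is unstratified while allocation is blocked by sex and meant to be balanced by centre.

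The effect on the primary outcome is about 0–1 point of power, with no bias and no change to the 2,319 per arm. For a 10% outcome with strong centre differences it is about 1–3 points. These sizes depend on centre and sex effects that the article does not give. The direction (no material loss, some possible gain) held in every setting examined, apart from differences within simulation error.

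Differing control-arm practice is a separate matter, and this change does not resolve it.

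**What to change.** 1. In {20a}, state that the arms are compared by a Mantel-Haenszel risk difference with the Cochran-Mantel-Haenszel test, stratified by sex and centre, at each planned time point. Fix a rule for pooling very small centres before the data are analysed. If the analysis plan already does this, a cross-reference is enough.
2. Use the same strata for invasive procedures and adverse events.
3. Resample within the same strata in the cost-utility analysis, drawing each stratum at its own size. The stated draw of 100 patients per group would leave 100 / 60 ≈ 1.7 per stratum, so the draw size has to be reset as well.
4. In {16a}, say whether centre is a formal stratum or only a balance aim.
5. Separately, reconcile the Discussion's plan to redefine the control protocol with the conventional schedule in {11a}. Which of them should govern is not for this review to say.

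The cost is wording in the protocol or analysis plan. Allocation is already meant to be balanced by sex and centre, so both should be on record; no new data or additional participants are needed.

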### Sample size {14}

The incidence of NADCs in the previous studies SMART and ESPRIT in virologically suppressed patients with CD4> 350 and over 40 years old was approximately 0.04% during 5 years of follow-up [27]. An Italian study described an incidence of NADCs of 0.67 per 100 person-years of follow-up [28]. In the CoRIS cohort, with 31.228 person-years of follow-up, a total of 136 NADCs were diagnosed, and the incidence was 0.43 per 100 person-years of follow-up. In a study of lung cancer screening among smokers, the prevalence of lung cancer was 2.03% [29]. For the calculation of the sample size, we have estimated an incidence of cancer diagnosed at an early stage of 2% in in the intervention group and 1% in the control group. With a statistical power of 80% and a loss to follow-up percentage of 20%, it is estimated that for a unilateral contrast it would be necessary to include 2.319 subjects in the exposed group (enhanced intervention) and 2.319 in the unexposed group (standard intervention) (1:1), with a total sample of 4.638 patients.

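### The all-consented analysis set and the rule to ignore missing observations are not reconciled for participants lost without a recorded cancer, and the per-protocol set is selected on survival and retention

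*Protocol article*

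**What the plan says.** All the rules at issue stand in one paragraph of the protocol article, Statistical methods for primary and secondary outcomes {20a}.

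- The primary set follows an intent-to-screen principle, "defined as patients who accept to participate in the study and sign the informed consent, regardless of whether they are subsequently excluded". The listed reasons for later exclusion include loss to follow-up, non-adherence, unwillingness to continue and death.
- On missing data there is one sentence: "Missing observations in the variables will be ignored in the analysis".
- On the supporting set: "A per protocol analysis including patients who complete the study will also be performed".

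Outcomes {12} defines the primary outcome as a new stage 1 or 2 NADC, "compared as the proportion between intervention groups at 12, 24, and 36 months". Sample size {14} plans for 20% loss to follow-up. Plans to promote participant retention {18b} adds a partial safeguard: "The protocol includes a form with a list of outcome data to be collected for participants who discontinue or deviate from intervention protocols". The sensitivity analyses in {20b} concern the economic and survival model, quality of life, operative mortality, costs and discounting. None addresses a missing primary outcome.

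**The concern.** Take a participant lost at month 10 with no cancer recorded. The 36-month outcome is unknown. The set definition says this person counts; the missing-data sentence can be read as saying that the person does not. These are rules that the article itself states, so this is not a detail left to an analysis plan.

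The choice matters because the outcome is observed asymmetrically. A cancer diagnosed before loss is known, whereas a lost participant without a diagnosis is unknown. Dropping the unknowns therefore removes apparent non-cases and raises the proportion. Keeping them as non-cases misses cancers that arise after loss and lowers it. If loss differs by arm, either choice shifts the comparison, in opposite directions. Expected events are few next to expected losses, so the rule could influence the result.

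The completer set raises a separate problem. Completing the study is a post-randomisation event that requires survival, so the set leaves out people who die of cancer.

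**Working it through.** **Inputs from the protocol.** 2,319 per arm, 4,638 in total; early-cancer incidence 2% versus 1%; 80% power; one-sided; 20% loss ({14}). Significance level 0.05 ({20a}).

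**The plan's own figure.** The standard one-sided two-proportion formula gives 1,826 per arm; 1,826 / 0.8 = 2,283, which is 1.6% below the stated 2,319. The stated size is therefore broadly consistent with its inputs.

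**Losses against events.**
- Expected losses: 0.20 × 4,638 = about 928.
- Expected early cancers: 1,855 × (0.02 + 0.01) = about 56 if only the 80% retained contribute (0.8 × 2,319 = 1,855), or 2,319 × 0.03 = about 70 over the full set.

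**Effect of the two readings.** Assumptions not in the protocol: true 36-month risk r = 1.5% in both arms; loss L = 25% enhanced, 15% control; lost participants have the same risk as the rest; a share s of their cancers is recorded before loss.

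- Kept as non-cases: p = r(1 − L + Ls)
- Dropped if unknown: p = r(1 − L + Ls) / (1 − L + Lrs)

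With s = 0.5:
- Kept: 0.015 × 0.875 = 1.31% versus 0.015 × 0.925 = 1.39%; difference −0.075, about −0.08 points.
- Dropped: 0.013125 / 0.751875 = 1.75% versus 0.013875 / 0.851125 = 1.63%; difference +0.12 points.

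Rejection under dropping is 1 − Φ(1.645 − d/SE). For s = 0.5 the denominators are about 1,744 and 1,974, SE = 0.424 points and d/SE = 0.27, which gives 8.5%.

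| Share seen before loss | Dropped: difference (points) | One-sided rejection | Kept as non-cases: difference (points) |
|---|---|---|---|
| none | 0 | 5.0% | −0.15 |
| a quarter | +0.06 | 6.6% | −0.11 |
| half | +0.12 | 8.5% | −0.08 |
| all | +0.23 (1.99% vs 1.76%) | about 13% | 0 |

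Reversing the losses to 15% / 25% reverses every sign. With 20% in both arms and equal true rates, both readings give a difference of zero.

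For a true 2% versus 1%, loss 25% / 15% and half seen, the estimated difference is 0.83 points if the lost are kept (1.75% vs 0.925%) and 1.24 points if they are dropped (2.33% vs 1.09%), against a true 1 point.

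**Completer set.** Assumed cancers: 46 early and 12 late (enhanced), 23 early and 23 late (control), with half of the late cases dying before month 36.
- All cancers: 46/58 = 79% versus 23/46 = 50%; difference 29 points.
- Completers: 46/52 = 88% versus 23/34.5 = 67%; difference 22 points.

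The early-stage share rises in both arms, and the difference changes, purely through removal of deaths.

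**The case against.** The strongest reply is that the set definition is explicit: participants stay in "regardless of whether they are subsequently excluded due to loss of follow-up, non-adherence to study procedures, unwillingness to remain in the study, death, etc". On that view the missing-data sentence concerns incomplete variables, and the lost remain in the denominator. This reading is possible, so a reader who infers that the plan definitely drops the lost goes beyond the text. It does not settle the matter, because keeping the lost as non-cases is also biased when loss differs by arm, and the article never says that this is the rule.

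A reader might also infer a bias in favour of enhanced screening, on the ground that this arm has twice the visits and so more loss. The documents do not support that. In Table 1 the six-monthly marks in the enhanced arm apply only to the liver, anal and cervical tests, and co-tested women are seen annually. The conventional arm's liver ultrasound is itself described as semi-annual, and all participants are in routine HIV care. The article gives one overall loss figure and none by arm.

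The +0.23 points and 13% are the upper end for the assumed loss pattern, because they require every cancer in lost participants to be recorded before loss. The discontinuation form in {18b} should reduce the number of unknown outcomes, but it gives no rule for those that remain.

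The completer example concerns the early-stage share, which is secondary outcome 2. It does not show bias in the primary comparison, and per protocol is only an additional analysis. In the two-arm example the selection works against the intervention.

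A reader might add that the comparison disregards the sex and centre restriction used in randomisation. The article names no test or model for the primary comparison, and that choice is properly left to the analysis plan, so it is no part of this point.

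**Conclusion.** The point holds as an unreconciled pair of stated rules, together with a poorly chosen per-protocol set. Neither the direction nor the size of the resulting bias can be known from the protocol. In the 25% / 15% illustration the spurious difference runs from −0.15 to +0.23 points across the two readings and the full range of s, against a planned effect of 1 point. One-sided rejection under dropping runs from 5% to about 13%. These figures rest on assumed arm-specific losses and on equal risk in lost and retained participants; with equal loss and equal true rates the spurious difference is zero. Confidence is high in the conflict itself and in the selection within the completer set, but low in any particular magnitude. The change should be made before analysis.

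**What to change.** 1. Delete the sentence on ignoring missing observations.
2. Define the primary set as all randomised participants, analysed as allocated.
3. Estimate the cumulative incidence of a first stage 1–2 NADC at 12, 24 and 36 months, with censoring at last contact and death as a competing event. Use outcome data from the discontinuation form.
4. Add a sensitivity analysis for unknown outcomes, with assumptions that may differ by arm, because censoring still assumes that loss is non-informative.
5. Define per protocol by adherence to the scheduled screening tests, and never exclude a participant for death or cancer.

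The cost is revised wording and modest programming. Dates of diagnosis and of last contact must be captured. The article mentions a form listing outcome data but does not say that these dates are on it, so this has to be checked and, if needed, added.

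### The 95% interval planned around the cost-utility ratio names no quantity or method, and an interval for the ratio itself would mislead if the QALY difference is not clearly away from zero

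*Protocol article*

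**What the plan says.** Cost-utility is the third specific objective, and cost-effectiveness is part of the stated hypothesis. Section 20a of the protocol article fixes the summary measure: "The incremental cost-effectiveness ratio will be calculated, which is a measure of contrast between the increase in costs and the increase in effectiveness". The next sentence is "Statistical uncertainty will be expressed as the 95% confidence interval". It does not say what the interval is for or how it is built.

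The same paragraph continues: "Random samples of 100 patients from each group replaced 10,000 times will be projected on a graph", to generate the QALY increment, "the increase in costs, and the cost-effectiveness curve". For the probabilistic sensitivity analysis, section 20b says "the results will be presented as a dispersion analysis (cost-effectiveness plan) and the acceptability curve". Net benefit, a willingness-to-pay threshold, and what to report when the QALY difference spans zero are not mentioned.

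Three other places bear on the likely size of the QALY difference:
- Sample size {14} assumes "an incidence of cancer diagnosed at an early stage of 2% in in the intervention group and 1% in the control group".
- The Discussion concedes that "with our sample size, we will not reach the number of patients needed to detect differences in mortality between both groups".
- Section 22 lists complications of invasive procedures among the harms to be expected.

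**The concern.** The ratio is the only estimate named before the sentence on uncertainty, so most analysts would take it as an instruction to put an interval on the ratio. That is sound when the denominator is clearly positive. When the denominator can change sign, the ratio loses its order.

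Take an extra cost of 600 (an assumed figure) and four possible QALY differences. In ascending order the ratios are:
- loss of 0.001: −600,000
- loss of 0.01: −60,000
- gain of 0.01: +60,000
- gain of 0.001: +600,000

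The two nearly identical results (±0.001) sit at opposite ends, and the larger loss ranks as less extreme than the trivial one. A saving of 600 with a gain of 0.01 also gives −60,000, the same value as the result that costs more and does harm.

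A negative lower limit invites the reading that the programme may save money, when it may come from replicates in which the programme costs more and loses QALYs. That would mislead on a named objective.

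**Working it through.** **Inputs from the article.** Early-cancer rates 2% and 1%; 2,319 per arm; 20% loss; 80% power; one-sided test; draws of 100 per group, 10,000 times.

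**Inputs assumed, because the article gives none.** QALY gain per extra early cancer 0.5 to 5; per-person QALY SD 0.2 to 0.6; extra cost 600 with SD 2,000; threshold 25,000 per QALY.

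**The plan's own figure.** The cost-utility text states no number that can be checked. The arm size can be: with mean rate 0.015, n = [1.645·√(2·0.015·0.985) + 0.842·√(0.0196 + 0.0099)]² / 0.01² ≈ 1,826, and 1,826/0.8 ≈ 2,283. That is within 2% of 2,319, and nothing below turns on the difference.

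**Step 1: chance of a negative QALY difference.** Mean difference = 0.01 × gain per case. SE = SD × √(2/n). P(negative) = Φ(−difference/SE). At n = 2,319, √(2/n) = 0.0294. For gain 1 and SD 0.3, SE = 0.0088 and P = Φ(−0.010/0.0088) = 12.8%.

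**Step 2: how often the percentile interval for the ratio has a negative lower limit.** 1,500 simulated trials, each with 2,000 bootstrap draws at full arm size (normal approximation):

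| Gain per extra early case | SD | P(QALY difference < 0) | Trials with lower limit < 0 |
|---|---|---|---|
| 0.5 | 0.6 | 38.8% | about 95% |
| 0.5 | 0.3 | 28.5% | about 92% |
| 1 | 0.6 | 28.5% | about 91% |
| 1 | 0.3 | 12.8% | about 79% |
| 3 | 0.6 | 4.4% | about 61% |
| 3 | 0.3 | under 0.1% | about 8% |
| 3 | 0.2 | under 0.1% | about 0% |

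A gain of 3 QALYs per case is the most that can accrue within 36 months. With 20% loss (2,319 × 0.8 ≈ 1,855 per arm) the probabilities rise slightly: for gain 1 and SD 0.4, from 19.7% to 22.3%.

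**Step 3: two worked cases at 2,319 per arm, extra cost 600.**
- Gain 1, SD 0.4: point ratio 600/0.01 = 60,000; percentile interval about −490,500 to 566,900. Every replicate in the lowest 2.5% costs more and loses QALYs. Net benefit is 25,000 × 0.01 − 600 = −350, with interval −922 to 234, which can be read directly.
- Gain 3, SD 0.2: point ratio 600/0.03 = 20,000; interval about 13,600 to 33,300, which is well behaved.

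**Step 4: the 100-patient draws.** Drawing 100 instead of 2,319 multiplies the SE by √(2,319/100) = 4.8. P(negative) then runs from 0.04 to 0.48 over SD 0.2 to 0.6 and gain 0.5 to 5, above 2.5% in every combination. On the plan's own rates, 100 enhanced patients have strictly fewer early cancers than 100 conventional ones in 18% of draws, against 0.2% at 2,319.

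**Step 5: the alternative.** With draws at full arm size, the 95% interval for net monetary benefit covered the true value in about 94% to 96% of simulated trials.

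**The case against.** The strongest reply is that the article never tells anyone to sort ratios. The sentence could mean an interval for each increment, which fits the sentence that follows it, or a Fieller interval. Construction details often sit in an analysis plan or in the Spanish economic-evaluation guide that section 20a invokes. This stands as far as the method goes, and so the percentile interval is a natural reading rather than a stated rule. It does not clear the sentence: if each increment was meant, one clause settles it, and Fieller's method gives an unbounded set when the QALY difference is not significantly different from zero.

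Second, the inputs are assumed and the result swings with them. That stands, and is why the size is given as a range.

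Third, section 20b describes a model with long-term survival and discounting, so within-trial QALYs may not be the endpoint. This also stands. Under an assumed lifetime SD of 4 to 8 and a gain of 5 to 10 QALYs per case, 20% to 42% of replicates are negative. But that treats patient-level spread as the sampling error, which a decision model need not do, and no interval-failure rate was computed for it.

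Fourth, the planned plane and acceptability curve show the quadrants and do not misrank harmful replicates. That is correct, and they should stay. They sit beside a published ratio interval without correcting it.

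**Conclusion.** The point holds in conditional form. Section 20a pairs a ratio with an unspecified 95% interval, and an interval for the ratio would be disordered whenever the QALY difference is not clearly away from zero. The article's own statements on effect size, mortality and harms make that plausible. With 2,319 per arm the negative lower limit appears in roughly 0% to 95% of trials, depending on an assumed QALY SD and gain per case. It appears in over 90% of the cases tried if the interval comes from the 100-patient draws.

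A reader might infer that the interval is bound to fail, or that the whole cost-utility result cannot be read. The documents support neither. The quantity and method are not named, a clear QALY gain gives a usable interval, and the plane and curve remain valid. This is a secondary analysis with no decision rule tied to the interval, so the change is worthwhile but does not affect the trial's primary conclusion.

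**What to change.** In section 20a, replace the sentence on uncertainty with wording such as: *Uncertainty will be expressed as 95% confidence intervals for incremental cost, for incremental QALYs and for incremental net monetary benefit at the stated willingness-to-pay threshold(s). The ratio will be reported as a point estimate, and no interval will be given for it when the interval for incremental QALYs includes zero.* Keep the plane and the acceptability curve.

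The intervals should come from draws at full arm size. The 94% to 96% coverage applies to those; in the first worked case the net-benefit interval from 100-patient draws would run from −3,166 to 2,513 instead of −922 to 234.

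The cost is a few lines of text and no new data. A threshold has to be named in advance, and the result may look less decisive than a single ratio.
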